## Abstract

**Background:**

The acute abdomen is a frequent entity at the Emergency Department (ED), which usually needs rapid and accurate diagnostic work-up. Diagnostic work-up with imaging can consist of plain X-ray, ultrasonography (US), computed tomography (CT) and even diagnostic laparoscopy. However, no evidence-based guidelines exist in current literature. The actual diagnostic work-up of a patient with acute abdominal pain presenting to the ED varies greatly between hospitals and physicians. The OPTIMA study was designed to provide the evidence base for constructing an optimal diagnostic imaging guideline for patients with acute abdominal pain at the ED.

**Methods/design:**

Thousand consecutive patients with abdominal pain > 2 hours and < 5 days will be enrolled in this multicentre trial. After clinical history, physical and laboratory examination all patients will undergo a diagnostic imaging protocol, consisting of plain X-ray (upright chest and supine abdomen), US and CT. The reference standard will be a post hoc assignment of the final diagnosis by an expert panel. The focus of the analysis will be on the added value of the imaging modalities over history and clinical examination, relative to the incremental costs.

**Discussion:**

This study aims to provide the evidence base for the development of a diagnostic algorithm that can act as a guideline for ED physicians to evaluate patients with acute abdominal pain.

## Background

Acute abdomen is a common presentation in emergency medicine. It represents 5 to 10% of all Emergency Department (ED) visits [1,2]. Causes of acute abdominal pain can range from benign self-limiting conditions to acute life-threatening disorders. To provide appropriate triage and care, rapid and accurate diagnostic work-up is necessary.

No sufficient data are currently available in the literature to develop evidence-based guidelines for diagnostic imaging in patients with acute abdominal pain at the ED. Current diagnostic work-up shows wide variation in the use of imaging modalities, both between and within hospitals. Plain X-rays, ultrasonography and computed tomography are used, if used at all, solitary or combined in patient work-up. During the last decade, a trend towards increased use of computed tomography in patients with abdominal pain [3-5] can be seen. New questions concerning cost-effectiveness of imaging have been raised, with regards to both over-usage and under-usage of imaging.

Over-usage may have a negative impact on efficient patient throughput, costs and radiation exposure. Under-use may delay treatment, which in urgent conditions can increase morbidity and even mortality. Some physicians advocate diagnostic laparoscopy instead of imaging in patient work-up. Diagnostic laparoscopy has a high accuracy in highly selective patient series. Because of its invasiveness, costs and complications [6] laparoscopy is not suitable as an initial diagnostic tool in patients with acute abdominal pain at the ED when similar accuracy can be obtained without surgery.

Most research performed so far focused on diagnostic value of imaging for specific diagnosis. Imaging in acute appendicitis is a topic well-studied, but represents only 6 to 10% of ED presentations of abdominal pain [2,7]. The purpose of this study (OPTIMA trial) is to collect data for constructing an optimal diagnostic algorithm for the wide spectrum of patients with acute abdominal pain at the ED. Using this algorithm, decisions to perform further imaging can be based on patient characteristics, signs and symptoms at presentation without compromising health care by missing relevant diagnosis or delaying treatment. Optimizing usage of imaging modalities will reduce costs and may allow the development of an evidence-based guideline for patients presenting with acute abdominal pain at the Emergency Department.

## Methods/design

### Study objectives

The study aims to develop optimal diagnostic algorithms for the acute abdomen, based on the added value of plain x-ray, US and CT over clinical history, physical and laboratory examination. Furthermore, we will perform a cost-effectiveness analysis of imaging use.

### Study design

OPTIMA is a fully paired diagnostic accuracy study, with a complete diagnostic protocol for patients with acute abdominal pain. All included patients will undergo an abdominal and chest X-ray, abdominal ultrasound and a CT abdomen with intravenous contrast medium. The reference standard is the final diagnosis assigned by an expert panel with all individual information available including 6 months of follow-up.

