### Diagnostic tests

Initial examination will consist of standardized clinical history, physical and laboratory examination. Subsequently, a supine abdominal X-ray, an upright chest X-ray, an abdominal ultrasound and a spiral CT scan will be performed.

The diagnostic tests are also performed in a standardized way. Abdominal ultrasound scanning will systematically investigate the entire abdomen for general and organ specific anomalies. Both positive and negative findings will be recorded of all variables listed in the case record form. A curved 3.5 – 5.0 MHz array and a linear 10 MHz array will be used.

All abdominal CT scans will be performed using a multi-detector row 4 or 16 slice helical CT scanner (SOMATOM Sensation 16 and SOMATON plus; Siemens Medical Systems, Forchheim, Germany; MX8000 and Tomoscan AV; Philips Medical Systems, Best, The Netherlands). The model CT scan protocol consists a scan with an effective mAs level of 165, and 120 kV, collimation: 2.5 mm, slice width: 3 mm, rotation time: 0.5s. Intravenous contrast (125 ml. Visipaque 320; Amersham Health AS, Oslo, Norway) will be injected at 3 ml/s. Scanning will start after 60 seconds. No oral or rectal contrast agents will be used.

All results, including findings and diagnosis after initial examination, will be recorded independently of previous results and other findings. Case Record Forms (CRF) will facilitate the standardization of clinical history, physical examination, laboratory parameters and radiological examination. After clinical history, physical and laboratory examination the three most likely diagnoses, a level of confidence of the most likely diagnosis and a management plan will be recorded by the treating physician. Subsequently, a differential diagnoses, level of confidence of the most likely diagnosis and a management plan will be recorded separately after plain X-ray, after US and finally after CT (Figure 1).

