**Figure 1 F1:**
[figure not shown]
shows the OPTIMA study flow chart.

Chest and abdominal X-rays will be evaluated by the treating physician. Both US and CT are performed and evaluated by radiological residents or radiologists, blinded for each others test results and for the test results of the abdominal and chest X-rays. Summarized clinical findings, as in routine practice, will be provided to the radiologist. The radiologist performing the ultrasound will record the findings in the patients CRF with general and organ-specific US findings ending with a differential diagnosis with a level of confidence of the most likely diagnosis. Another radiologist evaluates the CT scan and records data in a similar way.

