### Outcome measures

#### Follow up

Six months of follow up will be obtained for all patients. All available information will be gathered, including course of disease, laboratory findings, operation reports, pathology reports, treatment outcome and costs.

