#### Reference standard

All included patients will be evaluated using a uniform reference standard not dependent of the index tests results. An expert panel will review each case and assign the final diagnosis. Cases will be presented in a standardized way, including all available follow-up data gathered as mentioned above. Panel members will evaluate cases individually, after which consensus is reached in group discussion. These final diagnoses will be classified as urgent, defined as a diagnosis which requires treatment within 24 hours, or as non-urgent. The distribution of conditions based on urgency is presented in table 1.

**Table 1 T1:** Urgency classification of diagnoses

**Urgent**	**Non-urgent**
Acute appendicitis	Cholecystolithiasis
Acute diverticulitis	Obstipation
Perforated vicus	Gastrointestinal disorders^∥^
Bowel obstruction/ileus	Hepatic disorders^¶^
Bowel ischemia	Malignancy**
Inflammatory bowel disease	Gynaecological disorders^††^
Peritonitis	Renal and urinary tract disorders^‡‡^
Acute cholecystitis	Non-specific abdominal pain
Cholangitis	
Pancreatitis (acute and chronic)	
Abscess*	
Renal and urinary tract disorders^†^	
Gynaecological disorders^‡^	
Extra-abdominal disorders^§^	

* Intra-abdominal abscess, retro-peritoneal abscess, hepatic abscess, tubo-ovarian abscess

^† ^Renal and ureteral stones with obstruction, hydronephrosis, pyelonephritis

^‡ ^Adnexal torsion, pelvic inflammatory disease, bleeding/rupture ovarian cyst

^§ ^Pneumonia, myocardial infarction, mediastinitis

^∥ ^Gastritis, gastroenteritis, peptic ulcer, acute epiploic appendagitis

^¶ ^Hepatitis, hepatic metastases

** Pancreatic, intestine and kidney malignancies

^†† ^Ovulation pain/bleeding, endometriosis, menstrual pain, uterine myoma

^‡‡ ^Renal and ureteral stones without obstruction, urinary tract infection

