## Discussion

### Rationale behind the study design

An alternative, possibly preferable study design is that of a randomised control trial (RCT). However, comparing all possible and daily used diagnostic strategies will need numerous trial arms with large amounts of patients and therefore is not practically feasible. Randomising patients to diagnostic strategies that are not evidence-based exceeds our study objectives. Our study is designed to collect evidence to provide guidelines for such diagnostic strategies. Therefore we chose this design which contains a full, probably over-complete, diagnostic protocol of 1,000 consecutive patients. Comparing imaging modalities separately as well as subsequently is possible because of stepwise and independently recording of the diagnosis, level of confidence of the diagnosis and a management plan after each diagnostic step.

The accurate detection of urgent conditions will lead to better therapeutic decision making. By making this a basic premise in our statistical analysis we believe that the optimal diagnostic strategy will lead to the health gains. However, our design prevents an empirical comparison of the health outcomes of different strategies. Because of our complete diagnostic protocol it does not allow us to document consequences in patient outcome in case of false positive or false negative radiological findings. A RCT would allow us to estimate these outcome consequences, but at the price of a major limitation in the number of comparable strategies.

The reference standard in a diagnostic study is generally a challenge, because patients with a positive index test tend to receive a different reference test (e.g. surgery) than patients with a negative index test (e.g. clinical follow-up). This verification bias can lead to overestimation of the diagnostic test accuracy. Therefore, we chose a uniform reference standard for all patients. By means of an expert panel, in which radiologists and surgeons experienced in acute abdominal conditions will assign the reference diagnosis post hoc.

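### The panel's reference diagnosis is described as independent of the index tests, yet the panel is given all patient information, so incorporation bias is left unaddressed

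*Protocol article*

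**What the plan says.** On what the panel receives, the Study design section says: "The reference standard is the final diagnosis assigned by an expert panel with all individual information available including 6 months of follow-up". The same section makes the three index tests universal: "All included patients will undergo an abdominal and chest X-ray, abdominal ultrasound and a CT abdomen with intravenous contrast medium".

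The Reference standard section then says: "All included patients will be evaluated using a uniform reference standard not dependent of the index tests results". It describes the case file as follows: "Cases will be presented in a standardized way, including all available follow-up data gathered as mentioned above". The Follow up section, to which this refers, says: "All available information will be gathered, including course of disease, laboratory findings, operation reports, pathology reports, treatment outcome and costs". Index imaging is neither listed there nor excluded.

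The blinding that is stated concerns the US and CT readers, who are "blinded for each others test results and for the test results of the abdominal and chest X-rays" (text under Figure 1). No blinding of the panel to the index tests is described. The Diagnostic tests section adds that "a management plan will be recorded separately after plain X-ray, after US and finally after CT".

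The section on the rationale behind the study design discusses one bias of the reference standard: "This verification bias can lead to overestimation of the diagnostic test accuracy. Therefore, we chose a uniform reference standard for all patients". It adds that radiologists and surgeons form the panel. Incorporation bias is not mentioned.

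**The concern.** On a plain reading, a panel that has everything known about a patient also has that patient's X-ray, US and CT results. The independence stated under Reference standard is then a property that the design lacks.

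The index tests can reach the reference diagnosis by two routes:

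- **Directly:** the panel reads the imaging result and is influenced by it.
- **Indirectly:** operation and pathology reports, and part of the clinical course, exist because of management that the imaging helped to decide.

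Where the panel follows a wrong CT call, a CT false negative is counted as a true negative and a CT false positive as a true positive.

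The whole analysis depends on this standard. The Data analysis section cross-classifies imaging findings with the urgency class taken from the panel diagnosis. Sensitivities, specificities, head-to-head comparisons and added value all follow from that. The plan prefers the cheaper and less burdensome strategy when performance is equal, and the Economic evaluation section expects some strategy with less imaging to match imaging in all. If the standard leans towards CT, a strategy without CT may fail to look equal for that reason alone. A larger sample does not remove such a bias.

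**Working it through.** **The plan's own figure.** The Sample size section anticipates a sensitivity of 80%, a 95% confidence level and a margin of 5 points. The Wald formula gives n = 1.96² × 0.80 × 0.20 / 0.05² = 245.85, rounded up to 246, as stated. At 25% urgent, 246 / 0.25 = 984, in line with the stated 1,000. With 250 urgent cases the half-width is 1.96 × √(0.16/250) = 4.96 points. This figure is for one sensitivity, not for a paired difference. It serves here only as a yardstick.

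**Illustration of the bias.** From the plan: 1,000 patients, 25% urgent, CT sensitivity 80%. Assumed: CT specificity 90%, US sensitivity 70% and specificity 90%. Also assumed: the panel adopts the CT urgency call in a share q of *all* patients, whether or not CT is right, and is otherwise correct. The article gives no value for q.

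True CT counts are 200 true positives, 50 false negatives, 75 false positives and 675 true negatives.

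- Patients the panel calls urgent: 200 + 50(1−q) + 75q = 250 + 25q
- Apparent CT sensitivity: (200 + 75q) / (250 + 25q)
- Apparent US sensitivity, errors independent of CT: [0.7 × 200 + 0.7 × 50(1−q) + 0.1 × 75q] / (250 + 25q) = (175 − 27.5q) / (250 + 25q)
- Apparent US sensitivity, all CT errors shared by US: (175 + 75q) / (250 + 25q)

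| q (all patients) | CT | US, independent | Gap | US, shared | Gap |
|---|---|---|---|---|---|
| 0% | 80.0% | 70.0% | 10.0 | 70.0% | 10.0 |
| 10% | 207.5/252.5 = 82.2% | 172.25/252.5 = 68.2% | 14.0 | 182.5/252.5 = 72.3% | 9.9 |
| 20% | 215/255 = 84.3% | 169.5/255 = 66.5% | 17.8 | 190/255 = 74.5% | 9.8 |
| 40% | 230/260 = 88.5% | 164/260 = 63.1% | 25.4 | 205/260 = 78.8% | 9.6 |

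Apparent CT specificity at q = 20% is (675 + 10) / (1,000 − 255) = 685/745 = 91.9%.

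**Two equally good tests.** With both sensitivities at 80%, both specificities at 80% to 90% and independent errors, the apparent CT–US difference is about 4 to 6 points at q = 10% (82.2 − 77.9 to 82.7 − 76.5). At q = 20% it is about 8 to 12 points (84.3 − 75.9 to 85.2 − 73.3).

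**What q means.** Adopting a correct CT call changes nothing, so q acts only through the 50 false negatives and 75 false positives. It is also a share of all patients. If half the patients had proof independent of imaging, and proof were unrelated to the CT result, 40% adoption among the rest would be q = 20% in the table.

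**The case against.** The independence sentence can be read charitably: the same procedure is applied whatever the index tests show. The rationale section argues in just that way, and on that reading the sentence does not contradict the Study design section. This stands as a possible meaning. It answers differential verification only, so incorporation remains unaddressed and the wording still promises more than the design gives. Nor does the rationale section say in so many words that the panel removes verification bias; it gives that bias as the reason for the choice.

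A reader might infer that the panel will largely take over the imaging diagnosis where there is no surgery or pathology. The article does not support that. Six months of follow-up may expose an error exactly where CT was wrong, which lowers the effective q. A wrong diagnosis within the same urgency class does not change the main analysis at all.

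A reader might also infer that US must be marked down and the ranking distorted in a known direction. That needs independent errors. Both tests examine the same abdomen and their readers receive summarized clinical findings, so shared errors are plausible. With fully shared errors the gap does not widen and apparent US sensitivity rises.

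Finally, an expert panel with full information is a deliberate choice where no single test suits every condition, and the full protocol may hold more detail on the panel. That weighs on severity. It does not reconcile the two statements in this article.

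**Conclusion.** The point holds in a limited form and should be fixed. The article gives the panel all patient information, does not withhold the index tests, and still describes the standard as independent of them. Incorporation bias is not addressed. The expected direction is upward for apparent accuracy. That CT gains most is an inference from its place last in the sequence, the management plan recorded after it and the radiologists on the panel; the article does not state it.

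The size is unknown. At 20% adoption across all patients, apparent CT sensitivity rises by 4.3 points, close to the 5-point margin. The CT–US gap lies between about 10 and 18 points against a true 10, according to how far the errors are shared. These figures rest on the assumed accuracies, on adoption unrelated to whether CT is right, and on a panel that is otherwise correct. They show that the bias could matter, not that it will have this size. The design itself is not invalidated.

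**What to change.** 1. State which index-test results, images or reports, the panel sees.
2. Correct the independence wording under Reference standard. In the rationale section, say that the uniform panel addresses differential verification only, and name incorporation bias as a limitation.
3. Have the panel record for each case its certainty and the source of proof: surgery or pathology, clinical course and follow-up, or index imaging only.
4. Pre-specify a sensitivity analysis of the modality comparison that excludes or reclassifies cases whose diagnosis rests only on index imaging. Note that the proven subset is itself selected. Temper any recommendation whose ranking depends on those cases.

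A first panel judgement without the ED imaging reports, in all cases or in a random subset, is an optional addition. It should not act as a veto: that file would still hold surgery and follow-up driven by imaging, and it is a weaker reference for conditions treated without surgery.

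The cost is one or two extra fields per case, one extra analysis and a less favourable claim about the reference standard. No patient undergoes anything further. The fields are best added before the panel meets, because the source of proof is hard to reconstruct afterwards.

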### Setting

Patients will be enrolled from 6 participating Dutch hospitals, including two university hospitals (Academic Medical Center, AMC and University Medical Center Utrecht, UMCU) and four large teaching hospitals (Antonius Hospital Nieuwegein (AZN), Onze Lieve Vrouwe Gasthuis (OLVG), Gelre hospital and Tergooi hospitals).

### Study group

A random selection of consecutive adult patients who are presented, by themselves or a general practitioner, to the emergency department with non-traumatic abdominal pain persisting for at least 2 hours and less than 5 days.

### Eligibility criteria

#### Inclusion criteria

- Patients with abdominal pain with a duration of > 2 hours and < 5 days presenting at the ED.

#### Exclusion criteria

- Age < 18 years.

- Pregnancy.

- Abdominal pain due to blunt or penetrating trauma.

- Hemorrhagic shock caused by gastrointestinal bleeding or ruptured aortic aneurysm.

- Patients in whom no imaging was warranted by the treating physician ánd who were subsequently discharged home from the ED.

### Ethics and informed consent

The independent medical ethics committee (MEC) of the initiating hospital approved our final protocol, after consulting the advisory board on radiation exposure. The radiation dose, related mostly to the CT-scan, is within the guidelines of the MEC. An abdominal CT scan, with an estimated effective dose of 10 mSv, raises the possibility of X-ray induced fatal cancer by 0.05%, in addition to a baseline life time risk of naturally induced fatal cancer of 20% in the US [8].

All five other participating hospitals gave their approval after assessing the local feasibility of this study. Written informed consent will be obtained from all patients.

### Diagnostic tests

Initial examination will consist of standardized clinical history, physical and laboratory examination. Subsequently, a supine abdominal X-ray, an upright chest X-ray, an abdominal ultrasound and a spiral CT scan will be performed.

The diagnostic tests are also performed in a standardized way. Abdominal ultrasound scanning will systematically investigate the entire abdomen for general and organ specific anomalies. Both positive and negative findings will be recorded of all variables listed in the case record form. A curved 3.5 – 5.0 MHz array and a linear 10 MHz array will be used.

All abdominal CT scans will be performed using a multi-detector row 4 or 16 slice helical CT scanner (SOMATOM Sensation 16 and SOMATON plus; Siemens Medical Systems, Forchheim, Germany; MX8000 and Tomoscan AV; Philips Medical Systems, Best, The Netherlands). The model CT scan protocol consists a scan with an effective mAs level of 165, and 120 kV, collimation: 2.5 mm, slice width: 3 mm, rotation time: 0.5s. Intravenous contrast (125 ml. Visipaque 320; Amersham Health AS, Oslo, Norway) will be injected at 3 ml/s. Scanning will start after 60 seconds. No oral or rectal contrast agents will be used.

All results, including findings and diagnosis after initial examination, will be recorded independently of previous results and other findings. Case Record Forms (CRF) will facilitate the standardization of clinical history, physical examination, laboratory parameters and radiological examination. After clinical history, physical and laboratory examination the three most likely diagnoses, a level of confidence of the most likely diagnosis and a management plan will be recorded by the treating physician. Subsequently, a differential diagnoses, level of confidence of the most likely diagnosis and a management plan will be recorded separately after plain X-ray, after US and finally after CT (Figure 1).

